### Recruitment and enrollment procedures

From the 16 clusters, a list of eligible participants was generated from the “pre-ART and ART Registers.” At each cluster, selected village healthcare workers (VHCWs) were asked to mobilize potential participants after receiving training on trial objectives and procedures, as well as confidentiality aspects. The research team then held a trial-orientation meeting with the potential participants plus their caregivers. After orientation and screening, participants and caregivers who opted to take part in the trial and provided written consent, plus assent to enroll, were booked for enrollment procedures and baseline assessments. Recruitment and enrollment in the intervention and control arms occurred concurrently. At enrollment, participants were informed that they would be allocated to either the intervention or the control arm and told which one they were allocated to afterwards. Recruitment started on 15 August 2016 and concluded on 31 March 2017.

### Quantitative data collection and management

At enrollment, participants complete a questionnaire using an interviewer-administered, computer-assisted personal interview (CAPI) with more sensitive questions likely subject to socially desirability bias self-administered using an audio-computer-assisted survey instrument (ACASI) [35, 36]. Questionnaire domains include: sociodemographic, socioeconomic, medical history, including history of opportunistic infections and hospitalization, HIV-testing history, ART history, information on clinic attendances, information on adherence (self-report), and psychological wellbeing. On completion of the questionnaire, all participants are asked to provide a finger-prick dried blood-spot sample for HIV viral-load testing and undergo a clinical exam to assess WHO stage. All viral-load test results will be returned to the clinic within 3 months to guide clinical care (in both the intervention and comparison arms). All trial participants are assessed by the research team, in addition to their routine clinic visits, after 48 and 96 weeks. At the follow-up visit, they will complete a shortened version of the questionnaire, have a finger-prick blood-spot sample taken for viral-load testing and have a physical examination to allow clinical staging.

#### Quantitative data analysis

Data collected using ACASI and CAPI is downloaded into a password-protected Access database. The data will be analyzed using Stata 14. Statistical analyses will be conducted and reported in line with Consolidated Standards of Reporting Trials (CONSORT) guidelines [37] including a flowchart. Baseline characteristics of enrolled participants and the number continuing through the trial, actively withdrawing, and passively lost to follow-up will be shown by arm. The outcome measures will be summarized at baseline, 48 and 96 weeks by intervention arm, using proportions or means (SD) as appropriate.

Analyses will be intention-to-treat. Analyses will be based on cluster-level summary measures, as individual-level regression methods do not perform robustly when there are relatively few clusters per arm, especially for stratified cluster randomized trials [38]. For binary outcomes, the impact will be estimated by the risk ratio (RR) and risk difference (RD). The stratum-specific risk ratios will be estimated as the ratio of the geometric mean risks between arms for each of the two strata, and the overall RR will be estimated as the weighted-average of these stratum-specific risk ratios. An approximate variance for the log of the mean risk in each arm will be estimated from the residual mean square from a two-way analysis of variance of community log-risk on strata and study arm. A 95% confidence interval (CI) for the RR will be estimated from this variance using a stratified *t* test with 14 degrees of freedom. Similarly, a 95% CI for the RD will be estimated from an analysis of variance of the mean risk on strata and study arm. For continuous outcomes, the measure of effect will be the mean difference between arms, analyzed in an analogous method based on mean scores in each facility.

Secondary planned analyses will examine the impact of the intervention separately by age group, gender, duration on treatment, with assessment of effect-modification of the intervention effect by facility type using a previously described method [39]. Pre-defined sensitivity analyses will include adjustment for baseline viral load and other variables imbalanced at baseline. We will conduct sensitivity analyses to investigate the effect of missing data by using multiple imputation, analyzed using an individual-level Poisson regression model, allowing for within-cluster correlation using generalized estimating equations.

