### Trial design

The trial is a cluster randomized controlled trial (cRCT). The clinic is the unit of randomization. Sixteen clinics were randomized to either enhanced ART-adherence support through the Zvandiri program or standard of HIV care in a 1:1 allocation (Fig. 1). Adolescents aged 13–19 years were recruited. Trial outcomes are assessed through a clinical, behavioral and psychological assessment conducted at baseline and after 48 and 96 weeks.

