### Randomization

Imbalance between arms was minimized by using restricted randomization and matching of clusters on size and number of people in HIV care. Sixteen clusters were allocated 1:1 to either the immediate intervention or the control arm. To maximize transparency and buy-in from key stakeholders, a public randomization procedure was undertaken on 5 July 2016 involving MoHCC, Community Advisory Board members, and district-level governance and medical representatives.

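### The 14 degrees of freedom for the risk-ratio interval is the unstratified value; the two-stratum analysis described leaves 13 or 12 (a minor error)

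*Protocol article*

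**What the plan says.** The relevant text is in the protocol article under Quantitative data analysis, with the design facts under Trial design, Sample size and Randomization.

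- **Design.** "Sixteen clusters were allocated 1:1 to either the immediate intervention or the control arm"; Trial design likewise gives a 1:1 allocation. That is 8 clinics per arm.
- **Unit of analysis.** "Analyses will be based on cluster-level summary measures", so each clinic contributes one value and there are 16 observations.
- **Strata.** The risk ratio in each stratum is the "ratio of the geometric mean risks between arms for each of the two strata". The plan then pools the two results: "the overall RR will be estimated as the weighted-average of these stratum-specific risk ratios".
- **Variance.** It comes from the "residual mean square from a two-way analysis of variance of community log-risk on strata and study arm".
- **Interval.** The 95% limits for the risk ratio rest on that variance and on a t "test with 14 degrees of freedom", which the plan calls stratified.

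The risk-difference interval is described as built similarly, from an analysis of variance on stratum and arm. Continuous outcomes follow an analogous method. Neither is given its own degrees of freedom.

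**The concern.** A t interval takes its degrees of freedom from the residual mean square that supplies its variance. The section commits to two strata and to a residual mean square from a model containing strata, then states the figure that belongs to a model without them. The three statements (two strata, an analysis of variance on stratum and arm, 14 degrees of freedom) cannot all hold with 16 clinics.

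This is a stated number for the primary analysis, so it is not a detail left to an analysis plan. With so few clusters, the degrees of freedom help define the test. Left as it is, the analyst must choose later between three reference distributions. If the strata are kept, the stated figure always errs in the anti-conservative direction.

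**Working it through.** **Inputs.** 16 clusters (Trial design, Sample size, Randomization); 2 arms; 2 strata and a 95% two-sided level (Quantitative data analysis). For the illustration: 35% v 18%, k = 0.25, 500 participants and 20% loss (Sample size), giving 500 × 0.8 / 16 = 25 per cluster.

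**Step 1: reproduce the plan's figure.** 16 − 2 = 14. This is the unstratified two-sample t test. In the models described, 14 would need 17 clusters (17 − 3) or 18 clusters (18 − 4). The document gives neither.

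**Step 2: count for the analysis described.**
- Additive two-way analysis of variance: 16 − 1 (mean) − 1 (arm) − 1 (stratum) = 13.
- Stratified t test with stratum-by-arm cells: 16 − 2 × 2 = 12.

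The rank of the two design matrices confirms 13 and 12.

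**Step 3: effect on the interval.** The log-scale width is proportional to the 97.5% point of t. Actual error when t(14) is used with ν true degrees of freedom is 2 × P(T_ν > 2.1448).

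| Degrees of freedom | t(0.975) | Ratio to t(14) | Two-sided error if t(14) is used |
|---|---|---|---|
| 14 | 2.1448 | 1.0000 | 5.00% |
| 13 | 2.1604 | 1.0073 | 5.14% |
| 12 | 2.1788 | 1.0159 | 5.31% |

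The stated interval is therefore 1 − 1/1.0073 = 0.7% or 1 − 1/1.0159 = 1.6% too narrow. Coverage is 94.86% or 94.69%.

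**Step 4: illustration at the planning values.** The variance of a cluster log-risk is (1 − p)/(p × 25) + k².
- Standard care: 0.65/8.75 + 0.0625 = 0.1368.
- Intervention: 0.82/4.5 + 0.0625 = 0.2447.
- Standard error of the log risk ratio: √[(0.1368 + 0.2447)/8] = 0.218.
- Risk ratio: 0.18/0.35 = 0.514.

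The 95% intervals are 0.322 to 0.822 (14), 0.321 to 0.824 (13) and 0.320 to 0.828 (12).

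**Step 5: does planned power survive?** The usual cluster-trial formula gives the clusters needed per arm:

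1 + (1.960 + 0.842)² × [0.35 × 0.65/25 + 0.18 × 0.82/25 + 0.0625 × (0.35² + 0.18²)] / 0.17² = 7.70.

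Eight are available, so the sample-size statement reproduces. Power from the noncentral t distribution is 81.2% (14), 80.7% (13) and 80.2% (12).

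**The case against.** **The slip could be in the strata.** The document shows that 14 and two strata disagree; it does not prove which is wrong. The strata are never named. Randomization speaks of a restricted allocation with clinics matched on size and HIV caseload, and does not say that it was stratified. If the analysis were in fact unstratified, 14 would be right. This stands as a condition: the interval is too narrow only if the strata are kept. But the analysis section relies on strata for the point estimate, the variance, the t test and the risk difference, so the single figure is the likelier slip.

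**12 should not be imposed.** The analysis of variance as worded names stratum and arm and no interaction, which points to 13. Calling the test stratified points to 12. Either is defensible if it matches the residual mean square used. This stands.

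**The effect is small.** This also stands, as Steps 3 to 5 show.

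**Two stronger readings are tempting.**
- *Pair matching.* A reader might infer from the matching that 7 degrees of freedom apply (t = 2.365, an interval about 10% wider, error 6.9% under t(14)). The analysis section specifies two strata, not eight pairs, so these figures do not describe the planned analysis.
- *Mismatched scales.* A reader might infer that risk ratios are averaged arithmetically while the variance is for log risk. The averaging sentence is shorthand that fixes no scale, and the text around it (geometric means, log-risk, variance of the log) fits log-scale averaging. That makes it a wording point, not a second error.

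**Conclusion.** The point holds as a minor error. The stated 14 does not follow from the two-stratum analysis in the same section; that analysis leaves 13 or 12 degrees of freedom. The consequence is an interval 0.7% or 1.6% too narrow on the log scale, and a two-sided error of 5.14% or 5.31%.

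This rests on 16 clusters contributing one summary each, on the two strata being kept, and on the usual t-test assumptions for cluster summaries. The illustrative intervals and power also assume 25 participants per cluster and the planning values.

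A reader might infer that the primary test is materially invalid or the trial underpowered. The figures do not support that: power stays at or above 80%, and only a result almost on the boundary would be reclassified. Extending the correction to the risk-difference and mean-difference intervals is an inference from their being built in the same way, since no degrees of freedom are stated for them.

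**What to change.** 1. Replace 14 by the residual degrees of freedom of the analysis of variance whose residual mean square is used: 13 if it is additive in stratum and arm, 12 if the stratum-by-arm term is included. State which model it is, and name the two strata.
2. Use the same degrees of freedom for the risk-difference and mean-difference intervals where they come from the same stratum-and-arm analysis.
3. As a clarification only, say that the overall risk ratio is the exponential of the weighted average of the stratum-specific log risk ratios, to match the log-risk variance.

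The cost is a line or two of wording and slightly wider intervals (0.7% or 1.6% on the log scale). No change to design, sample size or data collection is needed.

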### Sample size and potential power of the trial

The total sample size of 500 participants recruited from 16 clusters will provide 80% power to detect a difference in detectable viral load of 35% among participants in the standard-care arm versus 18% in the intervention arm assuming 20% loss to follow-up and a coefficient of variation (*k*) between clusters of 0.25 [34]. For secondary outcomes, the trial will have 90% power to detect, for example, a difference in non-complete attendance of 26% in the standard-care arm versus 10% in the intervention arm, and 80% power to detect a difference in mean SSQ-14 [30] score of 7.4 in the control arm and 4.8 in the intervention arm (standard deviation (SD) = 3.74).

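### The SSQ-14 severity score is compared on follow-up clinic means without its own baseline value, giving up precision that a pre-specified adjustment could recover if clinic differences persist

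*Protocol article*

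**What the plan says.** The Objectives section of the protocol article includes reducing the severity of anxiety and depression. The Outcomes section measures that severity with the SSQ-14 as a continuous score at 48 and 96 weeks, among the secondary outcomes. The sample size section states "80% power to detect a difference in mean SSQ-14 [30] score of 7.4 in the control arm and 4.8 in the intervention arm", with an SD of 3.74.

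The score is available at baseline. Under Trial design, "Trial outcomes are assessed through a clinical, behavioral and psychological assessment conducted at baseline and after 48 and 96 weeks". Under Quantitative data analysis, "The outcome measures will be summarized at baseline, 48 and 96 weeks by intervention arm".

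The main analysis of continuous outcomes is one sentence in Quantitative data analysis: "the measure of effect will be the mean difference between arms, analyzed in an analogous method based on mean scores in each facility". The method it refers back to is an analysis of variance of clinic-level summaries with strata and study arm as its only terms. Baseline adjustment appears only among the sensitivity analyses, for baseline viral load and for other variables found to be imbalanced.

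**The concern.** The main estimate for the SSQ-14 score makes no use of the participants' own baseline scores. Baseline SSQ-14 would be used only if it happened to look different between arms, and then only in a sensitivity analysis. Observed imbalance is a poor criterion for choosing a covariate. The reason to adjust is that the covariate predicts the outcome, and an earlier reading of the same scale is the natural candidate.

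With eight clinics per arm, the precision of this comparison is governed mainly by how much clinics differ from one another. Randomization was restricted and matched on clinic size and number in HIV care, not on mental health. If clinics that start with worse scores tend to stay worse, that part of the between-clinic variation could be removed with data the trial already collects. What is at stake is the width of the confidence interval for one of the trial's stated objectives. The primary outcome is not affected.

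**Working it through.** **Inputs** (Protocol article, Sample size and Randomization sections)

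- "The total sample size of 500 participants recruited from 16 clusters" and "Sixteen clusters were allocated 1:1 to either the immediate intervention or the control arm": 8 clinics per arm.
- "assuming 20% loss to follow-up": 500 × 0.8 / 16 = 25 analysed per clinic.
- Means 7.4 and 4.8 (difference 2.6), SD 3.74.
- Coefficient of variation k "between clusters of 0.25". This stands in the viral-load sentence; that it also applies to the SSQ-14 is an assumption.
- Two-sided 5% level, inferred from the planned 95% intervals.

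**Step 1: reproduce the stated power.** Clinics per arm = 1 + (1.96 + 0.842)² × [2·SD²/m + k²(μ₀² + μ₁²)] / (μ₀ − μ₁)².

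- Within-clinic term: 2 × 3.74² / 25 = 1.12.
- Between-clinic term: 0.25² × (7.4² + 4.8²) = 4.86.
- Sum: 5.98.
- Clinics needed: 1 + 7.85 × 5.98 / 2.6² = 7.94, against 8 available.

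Power with 8 clinics is Φ(2.6/√(5.98/7) − 1.96) = 80.3%. A noncentral t calculation gives 79.8% on 14 df and 79.4% on 13 df. The stated 80% is therefore the power of the unadjusted comparison, and k = 0.25 fits it.

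**Step 2: where the variance lies.** 4.86 / 5.98 = 81% is between clinics. The SE of the difference is √(5.98/8) = 0.865.

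**Step 3: formula for the possible gain.** If the baseline score correlates r with follow-up at clinic-mean level, the variance is multiplied by about (1 − r²). Power is then Φ(2.6/√(5.98(1 − r²)/7) − 1.96): 84% at r = 0.3, 90% at 0.5 and 98% at 0.7. The SE falls to 0.825, 0.749 and 0.618. This ignores the cost of estimating the slope, so it is a rough check on the simulation below.

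**Step 4: simulation of the two-stage analysis.** The simulated trials had 16 clinics of 25, with 4,000 to 5,000 trials per setting and a t test on 13 df. The correlations are assumptions. Ranges reflect separate runs.

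| Clinic correlation | Individual correlation | Power, unadjusted | Power, two-stage |
|---|---|---|---|
| 0.2 | 0.2 | 80% | 80-81% |
| 0.3 | 0.3 | 79% | 82-83% |
| 0.5 | 0.5 | 79-80% | 88-89% |
| 0.7 | 0.7 | 79% | 96-97% |
| 0.5 | 0.3 | 78-80% | 85-87% |
| 0.2 | 0.5 | 80% | 79% |
| 0.1 | 0.5 | 78% | 75% |
| 0 | 0.5 | 79% | 73% |

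With both correlations at 0.3, 0.5 and 0.7, the mean width of the 95% interval falls from 3.7 points to 3.5, 3.1 and 2.6. In the last row it rises from 3.65 to 3.88. Where type I error was checked it lay between 4.4% and 5.5%. The adjusted estimate was pulled toward zero by about 1-1.5%.

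**Step 5: chance baseline differences.** At mean 7.4, the SD of the baseline difference between arms is √(2 × [(0.25 × 7.4)² + 3.74²/25] / 8) = √(2 × (3.42 + 0.56) / 8) ≈ 1.0 point. Only the persistent part reaches the follow-up comparison: about 0.3, 0.5 or 0.7 point at persistence 0.3, 0.5 or 0.7, which is 12%, 19% or 27% of the 2.6-point target.

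**Step 6: dependence on k.** By the Step 3 formula, k = 0.20 gives 92% unadjusted and 94% at r = 0.3. With k = 0.30 it is 68% unadjusted, then 72%, 80% and 92% at r = 0.3, 0.5 and 0.7.

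**The case against.** The planned comparison is valid and delivers the power claimed for it, so adjustment is an optional gain. That is correct. A reader might infer that the 80% figure is wrong; Step 1 shows it is not.

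A reader might also infer that clinic differences at baseline bias the effect, or pass into it in full, so that a 1.0-point SD distorts the result by 38% of the target. The documents do not support this. Under randomization these differences average to zero, they carry over only as far as they persist, and the between-clinic residual that sets the confidence interval already reflects them. They are the precision argument in another form, not a second defect. Clinics were randomized before recruitment opened; whether enrolment differed by arm is a separate question that this point does not address.

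The gain rests on a correlation that the documents do not give, over 48 and 96 weeks. At 0.2 it is about one point of power and at 0.3 three to four. Two-stage adjustment can also do harm. Stage 1 fits one slope, driven mainly by individuals, and can over-correct clinic means if clinic differences do not persist. With individual correlation 0.5, break-even is near clinic correlation 0.2. This stands and must be weighed.

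Two further defences are weaker. The sensitivity analysis depends on observed imbalance and leaves the main estimate unadjusted. The unseen analysis plan may say more, but the article itself states both the main model and where adjustment belongs. The article's preference for cluster-level methods is no obstacle, since inference would still rest on 16 clinic values.

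**Conclusion.** The point holds as a moderate one: avoidable imprecision in the analysis of a secondary outcome. It is not an error in the power statement, not bias, and not a matter for the primary outcome. Adjustment is worth about 1 to 17 points of power when clinic and individual correlations are equal and lie between 0.2 and 0.7. It costs up to about 6 points if clinic differences do not persist at all while individual scores correlate at 0.5. A reader might infer that adjustment must help; that follows only if clinic-level persistence is not well below the individual correlation. The figures rest on k = 0.25 applying to the SSQ-14, on 25 analysed per clinic, and on the assumed correlations.

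**What to change.** For the SSQ-14 score at 48 and 96 weeks, pre-specify a two-stage cluster-level comparison as the main analysis:

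1. Regress each participant's follow-up score on their own baseline SSQ-14 score and the strata, without arm.
2. Compare the clinic mean residuals between arms with the planned analysis of variance and t test.

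Include the baseline score whether or not it looks imbalanced, and report the unadjusted mean difference beside the adjusted one.

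The change is to wording and a few lines of code, with no new data or participants. The costs to state are:

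- a simple fill-in for missing baseline scores, for example the overall baseline mean;
- shrinkage of the estimate toward zero by about 1-2%;
- a loss of power if clinic-level persistence is well below the individual correlation (about 79% to 73% at clinic correlation 0 and individual correlation 0.5).

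The sponsor should record the clinic-level persistence it expects, and why, when fixing this choice.

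### The multiple-imputation sensitivity analysis uses the kind of individual-level model that the same section rejects for few clusters, so a difference from the primary result cannot be cleanly put down to missing data

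*Protocol article*

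**What the plan says.** All of this is in the protocol article, mostly under Quantitative data analysis.

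- Main method: "Analyses will be based on cluster-level summary measures". The reason given is that "individual-level regression methods do not perform robustly when there are relatively few clusters per arm, especially for stratified cluster randomized trials".
- Missing data: "We will conduct sensitivity analyses to investigate the effect of missing data by using multiple imputation". The imputed data are then "analyzed using an individual-level Poisson regression model, allowing for within-cluster correlation using generalized estimating equations". This is the only missing-data analysis the article describes. It names no small-sample correction, imputation model or missingness assumption.
- Number of clusters (Randomization): "Sixteen clusters were allocated 1:1 to either the immediate intervention or the control arm", so 8 per arm.
- Size and expected loss (Sample size and potential power of the trial): "The total sample size of 500 participants recruited from 16 clusters will provide 80% power", "assuming 20% loss to follow-up", with k = 0.25 and risks of 35% v 18%.

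**The concern.** The section gives a general reason for avoiding a class of methods with this number of clusters, then adopts a member of that class for the same clinics without saying why the reason no longer applies.

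Two things follow. First, a GEE with the usual sandwich variance and a normal reference tends to give intervals that are too narrow with 8 clusters per arm. Second, moving from the primary to the sensitivity analysis changes three things at once: the handling of missing outcomes, the estimator (ratio of geometric means of clinic risks v a ratio of risks that weights individuals) and the standard error. A sensitivity analysis is read by comparison with the primary one, and here the comparison mixes these changes.

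Missing data are not a side issue at 20% loss. As an illustration, take 35% v 18% among the observed 80% and assume that missing control participants fail at 35%. The failure rates among missing intervention participants below are also assumptions:

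- 35%: intervention risk 0.8 × 0.18 + 0.2 × 0.35 = 0.214, RR 0.61
- 50%: 0.144 + 0.100 = 0.244, RR 0.70
- 100%: 0.144 + 0.200 = 0.344, RR 0.98

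A check on a question of this size should be easy to read.

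**Working it through.** **1. The plan's power figure reproduces.** Clusters needed per arm, unmatched design, two-sided 5% (assumed from the planned 95% CI):

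c = 1 + (1.96 + 0.842)² × V / (p0 − p1)², with V = p0(1−p0)/m + p1(1−p1)/m + k²(p0² + p1²).

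- m = 500/16 × 0.8 = 25
- V = 0.2275/25 + 0.1476/25 + 0.0625 × (0.1225 + 0.0324) = 0.00910 + 0.00590 + 0.00968 = 0.02469
- c = 1 + 7.85 × 0.02469/0.0289 = 7.70, rounded up to 8
- With 8 per arm: √(7 × 0.0289/0.02469) − 1.96 = 0.90, power 81.7%, against the stated 80%

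The inputs are therefore a fair basis for the simulation.

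**2. Simulation set-up.** 100,000 trials per scenario, 8 clinics per arm, beta-binomial outcomes with k = 0.25, and either 25 assessed per clinic or sizes of 10-40 (assumed). Three tests were compared:

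- Poisson GEE: log ratio of pooled arm risks, independence working correlation, uncorrected sandwich variance, critical value 1.96.
- Cluster-level t test: difference in mean clinic log-risk, pooled variance, 14 df as the plan states (0.5 added where a clinic had no events).
- Corrected GEE: sandwich variance × c/(c − 1) with c = 8, t on 14 df.

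**3. Type I error at nominal 5%.**

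| True risk, both arms | Clinic sizes | GEE | Cluster t | Corrected GEE | GEE model SE / true SE |
|---|---|---|---|---|---|
| 35% | 25 | 8.5% | 4.7% | 4.8% | 0.91 |
| 35% | 10-40 | 9.2% | 4.7% | 5.2% | 0.90 |
| 18% | 25 | 8.5% | 4.7% | 4.8% | 0.91 |
| 18% | 10-40 | 9.3% | 4.9% | 5.3% | 0.89 |

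Under the null the GEE log-RR is centred on zero. The fault lies in its interval and p-value, not in bias of the estimate.

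**4. At 35% v 18%, with no missing-data effect.**

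- Rejection: GEE 89.3% v cluster-level 77.7% with 25 per clinic; 88-89% v 74-78% across both size patterns.
- GEE was significant and the cluster-level test was not in 12-15% of trials.
- The GEE 95% CI for the log RR averaged 27-28% narrower.
- Centre of the RR: cluster-level exp(−0.732) = 0.48; GEE exp(−0.672) = 0.51. The ratio of the two true arm risks is 0.18/0.35 = 0.51.

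Not all of the gap in rejection is error. The corrected GEE, which holds about 5% under the null, rejects in 82.2% of trials. So 82.2 − 77.7 = 4.5 points reflect a more efficient estimator, and 89.3 − 82.2 = 7.1 points come from the missing correction. Both parts would appear as a difference between the primary and the imputed result, and neither concerns missing data.

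**The case against.** **Silence on a correction is not a decision against one.** This is fair. A condensed article may leave the correction to an analysis plan, and a simple one restores 4.8-5.3%. The 8.5-9% applies only if none is used. What remains is that the article itself gives the reason for distrusting such models and then fixes one without a safeguard. A correction alone would also leave the change of estimator in place.

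**The GEE point estimate is still informative, and this is only a sensitivity analysis.** Both are true. A reader might infer that the planned analysis cannot test whether missing data drive the result. That is too strong: the estimate is centred correctly under the null, and a large shift after imputation would be seen. But a move such as 0.48 to 0.51 can arise from the estimator alone, and the article plans no complete-case run of the same model to separate the two.

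**Non-random loss.** A reader might also infer that the plan assumes missing at random and ignores loss linked to failure, since the intervention acts on retention. The documents do not support this as an error. No missingness assumption is stated, and delta or tipping-point details are commonly left to a plan that is not shown. Known deaths already count as failures (Outcomes). The research team assesses all participants separately from routine clinic visits (Quantitative data collection and management), so leaving clinic care is not the same as a missing trial outcome. The RR scenarios given with the concern rest on assumed failure rates and show only why the question matters.

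**The simulation is not the planned analysis.** It uses complete data, without strata or imputation variance, and the unequal sizes are assumed. It measures the few-cluster problem, not the exact error of the imputed analysis.

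**Conclusion.** The inconsistency is real and limited to the missing-data sensitivity analysis. With 8 clinics per arm and k = 0.25, an uncorrected Poisson GEE has a type I error of about 8.5-9% against about 4.5-5% for the cluster-level test. At the design values it rejects about 11-14 points more often (89 v 78; 88 v 74), and its central RR is about 0.51 rather than 0.48 before any outcome is missing. A difference from the primary result therefore cannot be cleanly assigned to missing data, and the sensitivity analysis may look firmer than it is. The primary inference does not depend on this model and is unaffected. The sizes assume no small-sample correction, an independence working correlation, beta-binomial clusters and clinic sizes of 25 or 10-40.

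**What to change.** Preferred: in each imputed data set compute the clinic-level risks, apply the same stratified cluster-level analysis as for the primary result, and pool with Rubin's rules using degrees of freedom based on the cluster-level df. Only the handling of missing outcomes then differs from the primary analysis.

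Alternative: keep the Poisson GEE, state a small-sample variance correction with t-based inference, and run the complete cases through the same model. The imputed result is then compared with that run, not with the primary one.

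The cost is one or two sentences in the plan, a little programming and somewhat wider intervals; no new data are needed. A non-random scenario (a delta shift or tipping point by arm) would be a cheap addition if the full analysis plan lacks one, but that is a recommendation and not a correction of the document.
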